**7-2. Adverse events expected**

No particular adverse events are expected.

**7-3. Serious adverse events**

A serious adverse event is one of the following adverse events:

1. Death.
2. Life-threatening event.
3. Hospitalization or extension of hospital stay.
4. Permanent or significant disability/dysfunction.
5. Event(s) that cause birth defects in offspring.

**7-4. Adverse event reports**

If a serious adverse event occurs, the investigator must comply with the Wakayama Medical University Ethics Review Committee "Procedure for dealing with a serious adverse events in human medical research." The investigator should take appropriate measures regardless of the causal relationship with the study drug, and immediately report the contents in writing to the president of Wakayama Medical University. If an unexpected serious adverse event occurs, and if a direct causal relationship with the study cannot be ruled out, the president should promptly report to the Japanese Ministry of Health, Labor and Welfare.

**8. Outcome definition**

**8-1. Primary outcome**

The BIS-11 score reduction effect of eight weeks of mindfulness meditation.

**8-2. Secondary outcomes**

1. Questionnaires for clinical symptoms (week 0, week 2 and week 8)

1) Impulsivity scale: BIS-11.

2) Impulse control disorder scale: QUIP-RS-J.

3) QOL scale for Parkinson's disease: PDQ-8 .

4) Mindfulness scale: MAAS.

5) Depression and apathy: HADS.

6) Mental symptoms and care burden: NPI-Q.

2. Motor symptoms in Parkinson's disease (week 0, week 8)

1) MDS-UPDRS part 3.

2) Hohen-Yahr score.

3. Cognitive function (week 0)

1) Mini-Mental State Examination (MMSE).

4. MRI (week 0, week 8)

1) Resting-state functional MRI.

2) Voxel-based morphometry.

3) T1w / T2w ratio image.

**9. Inspection items and schedule**

**9-1. Inspection items and information to be reported**

- Demographics: age, gender, height, weight, medical history (duration, age at onset, etc.), medication, past history and complications, and cognitive function (MMSE).
- Motor symptoms: MDS-UPDRS, Hoehn-Yahr scale.
- Questionnaires: Impulsivity Evaluation Scale (BIS-11), Impulse Control Disorder Scale (QUIP-RS-J), Depression and Anxiety Evaluation Scale (HADS), QOL Evaluation Scale (PDQ-8), Mindfulness Evaluation Scale (MAAS) is performed after the observation period, 2 weeks and 8 weeks. If there are any caregivers, NPI- Q is also performed as an evaluation of psychiatric symptoms.
- MRI is performed twice: before the intervention and within 14 days after the end of the study.
- Evaluation of achievement rate of mindfulness meditation using implementation record (15 minutes, 6 or 7 days per week)

**9-2. Inspection / reporting schedule**

|  | Enrollment | Allocation | Post-allocation | | End of study |
| --- | --- | --- | --- | --- | --- |
| Timepoint | Within 70 days | 0 | Week 2 | Week 8 |  |
| Enrollment: |  |  |  |  |  |
| Eligibility evaluation | X |  |  |  |  |
| Informed consent | X |  |  |  |  |
| MMSE | X |  |  |  |  |
| Intervention: |  |  |  |  |  |
| Mindfulness Meditation |  |  |  |  |  |
| Evaluation: |  |  |  |  |  |
| BIS-11 | X |  | X | X |  |
| QUIP-RS-J | X |  | X | X |  |
| HADS | X |  | X | X |  |
| PDQ-8 | X |  | X | X |  |
| MAAS | X |  | X | X |  |
| Hoehen-Yahr | X |  |  | X |  |
| MDS-UPDRS part3 | X |  |  | X |  |
| NPI-Q | X |  | X | X |  |
| MRI | X |  |  |  | X |
| Diary evaluation |  |  | X | X |  |
| Adverse event |  |  |  |  |  |

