**5-3. Precautions**

1. Registration after the start of protocol treatment is not allowed in any case.
2. The investigators should contact the registration office if they have any questions.
3. Except in cases where consent is withdrawn, subjects will not be unregistered.
4. If incorrect registration or duplicate registration is found, the registration office is contacted immediately.
5. Intervention is started within 70 days of enrollment.

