**6. Procedure**

**6-1. Research flow**

We recruit patients with PD visiting our institute. We explain the purpose and methods of this trial, and request research participation. Participants are registered after written informed consent. After registration, participants are evaluated by cognitive test (MMSE), motor symptom evaluation (UPDRS part 3, Hoehn-Yahr), MRI, and questionnaire evaluations (BIS-11, QUIP-RS-J, HADS, PDQ-8, MAAS, NPI-Q). For cases with wear-off phenomenon, MMSE, UPDRS, and MRI should be performed in “ON” state. MRI can be skipped in difficult cases, such as for patients with claustrophobia.

Group mindfulness meditation sessions are performed once a week under the guidance of a professional clinical psychologist, including approximately 30 minutes of guidance and 15 minutes of mindfulness meditation. Mindfulness meditation includes body scans and controlled breathing. Participants are required to practice meditation daily for 15 minutes on 6 or 7 days per week. The participants are given instruction papers in each group session for daily home-based practice, and fill in an implementation record. Clinical evaluations are performed in week 2 and week 8, and MRI is conducted within 14 days after week 8 evaluation. Daily mindfulness meditation continues until the final MRI. For evaluation items and schedule, refer to “#9, Inspection items and schedule."

Concomitant prohibited drugs.

From the date of registration to the end of study, new additions and changes to antiparkinsonian drugs, antipsychotic drugs, and antidepressants are prohibited.

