**10-3. Primary outcome**

Calculate the two-sided 95% confidence interval for the BIS-11 change after 8 weeks and the *P*-value for the t-test. In addition, a summary statistic of the measured value and the amount of change at each time point is calculated.

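### The protocol gives conflicting times for the baseline BIS-11, and its schedule lets the 8-week change span anything from 8 to 18 weeks in a trial with no control arm

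*Protocol*

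**What the plan says.** Four places in the Protocol bear on when the pre-treatment BIS-11 is taken.

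- Section 9-2 (schedule): the time axis is "Timepoint | Within 70 days | 0 | Week 2 | Week 8". BIS-11 is marked under enrolment, week 2 and week 8. The cell at time 0 is empty, as it is for the other questionnaires, the motor scales and MRI.
- Section 8-2 (secondary outcomes, with BIS-11 as the first item): "Questionnaires for clinical symptoms (week 0, week 2 and week 8".
- Section 9-1 (items): the questionnaire battery "is performed after the observation period, 2 weeks and 8 weeks". The Abstract has the same timing.
- Section 6-1 (research flow): "After registration, participants are evaluated by cognitive test (MMSE", with the questionnaires later in the same sentence and no day fixed.

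The delay to treatment is set in section 5-3: "Intervention is started within 70 days of enrollment". The primary outcome in section 8-1 is "The BIS-11 score reduction effect of eight weeks of mindfulness meditation", and its analysis in section 10-3 is "Calculate the two-sided 95% confidence interval for the BIS-11 change after 8 weeks" with a t-test. Neither names the visit from which the change is counted. Section 3-2 describes a single-arm, open-label pilot.

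**The concern.** The primary estimate is a within-patient change, so the baseline visit is half of its definition. If the baseline is taken at enrolment and treatment starts weeks later, the change has two parts: what happened while waiting and what happened during the eight weeks of meditation. A control arm would show the first part separately. Here nothing does, and the t-test credits the sum to meditation.

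The waiting time can also differ between patients, so the change score would not cover the same period for everyone. Staff following different sections could measure the primary baseline at different points in the pre-treatment window. A later analysis plan can define a baseline from scores that exist, but it cannot recover a week-0 score that was never collected. Visit timing therefore has to be settled in the protocol.

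**Working it through.** **1. The timings side by side.**

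| Section | Time of pre-treatment BIS-11 | Gap to first session |
|---|---|---|
| 9-2 | Enrolment column, 70-day window; time 0 empty | 0 to 70 days |
| 8-2 | Week 0 | about 0 days, if week 0 is the start of treatment |
| 9-1, Abstract | After the observation period | short, if that period ends as treatment starts |
| 6-1 | After registration | not limited beyond section 5-3 |
| 8-1, 10-3 | Not stated | not stated |

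None of these sections asks for BIS-11 at enrolment and again at week 0, and none limits the gap between the baseline score and the first session other than through the 70 days.

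**2. The interval the schedule permits.** Inputs: 70 days (5-3), 8 weeks = 56 days (8-1), final MRI within 14 days of the week 8 evaluation (6-1).

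- Shortest baseline to week 8: 0 + 56 = 56 days = 8 weeks.
- Longest baseline to week 8: 70 + 56 = 126 days = 18 weeks.
- Longest baseline to week 2: 70 + 14 = 84 days = 12 weeks.
- Longest first to final MRI: 70 + 56 + 14 = 140 days = 20 weeks.

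**3. What the change score then estimates.** Expected observed change = mean change before the first session + mean change from the first session to week 8. Only the second term matches section 8-1. The document gives no value and no sign for the first.

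**4. The plan's own sample size.** Section 10-2 gives a change of -10.0, SD 8.0, smallest clinically significant change -5.0, two-sided 10% and 80% power. For a one-sample t-test on a difference of 5 with SD 8, the noncentral t gives power 81.6% at n = 18, the smallest n reaching 80%. The stated 18 is reproduced. Baseline timing does not enter the formula, so 18 and the target of 20 stand.

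**5. Illustration only.** Assume no true treatment effect, SD 8, n = 20, a test against 0 at two-sided 5%, and a mean pre-treatment shift d towards lower scores. The chance of a significant reduction is 1 - F(t), where t is the 97.5% point of the t distribution on 19 degrees of freedom and F is the noncentral t distribution with noncentrality d√20/8.

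| Assumed shift before treatment | Noncentrality | Chance of a significant reduction |
|---|---|---|
| 2 points upward | -1.118 | 0.1% |
| 1 point upward | -0.559 | 0.6% |
| none | 0 | 2.5% |
| 1 point downward | 0.559 | 7.7% |
| 2 points downward | 1.118 | 18.5% |

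At n = 18 the two downward rows become 7.2% and 16.9%. The table shows how sensitive a single-arm test is to small shifts. It does not show that such shifts occur.

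**The case against.** The strongest reply is that the document can be read as intending a late baseline. The enrolment column is headed by a window, not a day. Section 9-1 puts the questionnaires after the observation period, while section 3-5-2 puts the first MRI during it, so the questionnaires may be meant for the end of the wait. Week 0 in section 8-2 may simply mean baseline: MMSE is labelled week 0 there but stands under enrolment in section 9-2. The empty time-0 column is headed as an allocation step in a trial that allocates nobody, which suggests a generic template. All of this stands. It shows that the text is ambiguous, but it does not settle which reading applies.

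The reply also limits the likely drift. Section 4-2 requires stable medication before enrolment, section 6-1 bars changes from registration, and no BIS-11 threshold governs entry, so regression to the mean through selection on the score is not built in. Retest and expectation effects persist after a week-0 baseline. These points also stand: the fix removes only change that occurs before treatment.

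Three stronger readings are tempting, and the documents do not support them.

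- A reader might infer that the primary outcome is defined from week 0 and that the schedule breaks that definition. Week 0 appears only in the secondary list; section 8-1 names no baseline.
- A reader might infer that patients will typically be followed for 18 weeks, or that drift favours meditation. Eighteen weeks is a permitted maximum under one of several wordings, and drift could equally hide a benefit.
- A reader might infer a loss of power. If the SD of change were 8.7 instead of 8.0, power for a difference of 5 at two-sided 10% would be 76% at n = 18 but 79.7% at the planned 20. Nothing in the document links a longer interval to an SD of 8.7 for the change; that figure appears in section 10-2 as the spread of single scores.

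**Conclusion.** The concern holds as a conflict over the timing of the primary baseline. Sections 6-1, 8-2, 9-1 and 9-2 do not agree on one time, and sections 8-1 and 10-3 do not choose between them. Under the schedule combined with section 5-3, the change labelled as eight weeks may cover 8 to 18 weeks. With no control arm, any pre-treatment change in either direction enters the estimate.

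The interval is exact arithmetic and assumes only that BIS-11 may be taken on the day of enrolment, as the schedule allows. The size of any resulting bias cannot be derived from the document; the drift figures are assumptions and are not evidence of a biased result. This is a 20-patient pilot meant to inform a later trial, and the lack of a control limits causal claims wherever the baseline sits. The point should be fixed, but it does not invalidate the design.

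**What to change.** In section 9-2, mark BIS-11 and the other questionnaires at time 0, completed before the first group session. In sections 8-1 and 10-3, state that this BIS-11 value is the baseline for the primary 8-week change. Align sections 5-3, 6-1, 8-2 and 9-1, and the matching Abstract rows, to that time, and say what the observation period is and when it ends.

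If an enrolment BIS-11 is also kept, report the enrolment-to-week-0 change descriptively only. That interval would vary from 0 to 10 weeks between patients, against a fixed 8 weeks on treatment, so it is a weak untreated comparison and should not be tested against the treatment-period change.

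The cost is an edit to the table and text and, if the enrolment set is kept, one extra set of self-report questionnaires at a session the patient already attends. No change to the sample size follows.

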**10. Statistics**

**10-1. Population**

The analysis target population in this study is defined as follows: if necessary, the principal investigator, the research secretariat, and the principal data management will discuss and make a decision before fixing the data.

Among the registered patients, the cases excluding duplicate and erroneous registrations are defined as "all registered cases". The group excluding "non-qualified cases" from all registered cases is defined as "all qualified cases".

- Effectiveness analysis target population.

All eligible patients who have undergone protocol treatment even once, excluding those who were found not to meet the eligibility criteria for this study after enrollment.

- Safety analysis target population.

Of all enrolled cases, those who received some or all of the protocol treatment.

**10-2. Rationale for sample size**

No reports have investigated the effects of mindfulness meditation on the impulsivity of PD. A report of mindfulness training on adolescents’ impulsivity reported that the BIS-11 score before the intervention was 82.49 ± 10.27, but decreased to 71.2 ± 9.16 after the intervention. In our previous study, patients with PD had a BIS-11 score of 62.6 ± 8.7, and healthy subjects had a BIS-11 score of 56.6 ± 10.6. We hypothesize that the change in BIS-11 is -10.0 ± 8.0 and the smallest clinically significant change is -5.0 by mindfulness meditation. If the significance level is 10% on both sides and the detection power is 80%, a sample size of 18 cases is required. Supposing there will be some ineligible cases, the required number of cases was set to 20 cases. The number of patients with PD in the Department of Neurology at Wakayama Medical University Hospital is about 300 per year, so it is estimated that the target number can be registered. SAS 9.4 was used to calculate the sample size.

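### Protocol section 10-2 plans on a 10-point BIS-11 fall without squaring it with a 6-point PD–healthy gap, and leaves the null value unnamed; if -5 must be exceeded, the 80% power holds only at -10

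*Protocol*

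**What the plan says.** All the planning figures stand in one paragraph of the protocol, section 10-2 (Rationale for sample size).

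- It states that no study of mindfulness meditation and impulsivity in PD exists. For adolescents it reports that "the BIS-11 score before the intervention was 82.49 ± 10.27, but decreased to 71.2 ± 9.16 after the intervention".
- From the group's own earlier work, "patients with PD had a BIS-11 score of 62.6 ± 8.7, and healthy subjects had a BIS-11 score of 56.6 ± 10.6".
- The planning assumption is: "We hypothesize that the change in BIS-11 is -10.0 ± 8.0 and the smallest clinically significant change is -5.0 by mindfulness meditation".
- The result is: "If the significance level is 10% on both sides and the detection power is 80%, a sample size of 18 cases is required". The target is then raised to 20 to allow for ineligible cases.

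Section 10-3 plans a two-sided 95% confidence interval for the 8-week change and a t-test P-value. It does not say which value the t-test is against. Sections 4-1 and 4-2 set no minimum BIS-11 score for entry.

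**The concern.** A mean fall of 10 from 62.6 would leave treated patients at 52.6, which is 4.0 points below the healthy mean quoted in the same paragraph. The section does not comment on this. Its one cited effect comes from a population that started about 20 points higher, and entry is not restricted to patients with high scores, so the protocol gives no ground for expecting a baseline well above 62.6.

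This matters if the trial is meant to show a change larger than the smallest clinically significant one. The 80% power then depends on the -10. An effect that brought patients to the healthy mean would usually not be shown to exceed -5, and a useful effect might be read as a failure. Section 1-2 says that the results will serve as preliminary data for phase III, so the reading of such a result has consequences.

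**Working it through.** **Inputs (section 10-2).** Hypothesised change -10.0; SD of change 8.0; smallest clinically significant change -5.0; two-sided level 10%; power 80%; n = 18. PD mean 62.6, healthy mean 56.6. Adolescents 82.49 before and 71.2 after. Level of the planned interval (section 10-3): 95%, so 5% two-sided.

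**Method.** One-sample t-test of the change, noncentral t distribution with n - 1 degrees of freedom. With d the distance between the true change and the null value, the noncentrality is d × √n / SD. Power is the probability that |t| exceeds the critical value, which for 17 degrees of freedom is 1.740 at two-sided 10% and 2.110 at two-sided 5%.

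**Step 1: reproduce the stated 18.**
- True -10 against -5: d = 5, noncentrality 5 × √18 / 8 = 2.65, power 81.6%. The smallest n reaching 80% is 18, as stated.
- True -5 against 0: d is again 5, so n is again 18. Only the difference enters the formula.
- True -10 against 0: d = 10, and 6 patients would suffice. This is not what was planned.

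The first reading uses every stated input. The second leaves the -10 unused. The protocol does not decide between them.

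**Step 2: candidate true changes from the section's own figures.**
- PD–healthy gap: 62.6 - 56.6 = 6.0.
- Adolescent fall, absolute: 82.49 - 71.2 = 11.29.
- Adolescent fall, relative: 11.29 / 82.49 = 13.7%; applied to 62.6 this is 8.57, about -8.6.
- Planned fall: 62.6 - 10.0 = 52.6, and 52.6 - 56.6 = -4.0.

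**Step 3: power with 18 patients and SD 8 to show a change beyond -5.**

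| True change | d | Two-sided 10% | Two-sided 5% |
| --- | --- | --- | --- |
| -6 | 1.0 | 14% | 8% |
| -8.6 | 3.57 | 57% | 43% |
| -10 | 5.0 | 82% | 71% |

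The 14% (14.4%) includes rejections in the wrong direction; counting only those in the beneficial direction gives 12.8%. If the SD is varied from 6 to 10, as an assumption, the 14% becomes 18% to 13%.

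**Step 4: power with the same 18 patients against 0.**

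| True change | Two-sided 10% | Two-sided 5% |
| --- | --- | --- |
| -5 | 82% | 71% |
| -6 | 92% | 85% |

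**Step 5: what an observed -6 would look like.** With SD 8 and n = 18, the standard error is 8 / √18 = 1.886. The 95% interval is -6 ± 2.110 × 1.886, about -10.0 to -2.0. It excludes 0 and contains -5.

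**The case against.** The strongest objection is that the 14% depends on a null value that the protocol never states. Section 10-2 calls -5.0 a smallest clinically significant change, section 10-3 names no null, and the primary outcome is simply a reduction in BIS-11, for which zero is the ordinary reference. Against zero, a change of -6 would very probably be detected. This stands: the low figures hold only if -5 is the value to be exceeded.

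Second, the healthy mean is not a floor. With a healthy SD of 10.6, 52.6 lies about 0.4 SD below it (4.0 / 10.6), and nothing in the document says that training cannot take scores below an untrained healthy mean. The -10 also lies between the two ways of carrying over the adolescent effect, -11.3 absolute and -8.6 relative. This stands too. A reader might infer that the planning value is contradicted or impossible; the documents show only that it is optimistic and unexplained.

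Third, this is a single-arm pilot described as exploratory, with no success rule tied to -5. A reader might infer that a fully normalising effect would be declared negative. The protocol prescribes no such reading, and it reports the estimate and interval whatever the result. Nor would it be right to call every interval containing -5 inconclusive: the interval of -10.0 to -2.0 shows a reduction and leaves open only whether it exceeds -5.

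The gap between the 10% planning level and the 95% interval is a separate matter. The 5% figures are given here so that the restated power matches the planned analysis, not to add weight to this point.

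**Conclusion.** The point holds in conditional form. The -10.0 is unexplained beside a PD–healthy gap of 6.0 and a single cited effect from a much higher baseline. If -5 is the value to be exceeded, the stated 80% power is reached only at -10, and it is 57% at -8.6 and 14% at -6 (two-sided 10%; 43% and 8% at 5%). If the test is against 0, the 18 patients do not depend on the -10 at all, and power at -6 is 92% or 85%. On either reading, power at the planning difference is 71% at the 5% level that matches the planned interval, below the stated 80%.

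These figures assume 18 evaluable patients, an SD of change of 8.0 as stated, and a one-sample t-test. The -6 and -8.6 are scenarios built from the section's own figures, not estimates of the effect. The weakness lies in the justification and in the unnamed null; the number 18 itself is computed correctly.

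**What to change.** In section 10-2:

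1. Name the null value of the t-test, and use the same value in section 10-3.
2. Restate the power without relying on -10: 18 patients give 82% power at two-sided 10%, or 71% at the 5% level matching the 95% interval, to detect a mean change of -5, the smallest clinically significant change, against no change.
3. Add the power to show a change beyond -5: 14%, 57% and 82% for true changes of -6, -8.6 and -10 at the 10% level, and 8%, 43% and 71% at 5%.
4. Add a reading rule: an interval that excludes 0 but contains -5 shows a reduction whose clinical significance is unresolved, and it is not evidence of no benefit.

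The cost is one rewritten paragraph and the null value in section 10-3. The 18 patients and the target of 20 are unchanged. The downside is that the stated figures become less favourable.

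### The sample size uses a two-sided 10% level but the primary outcome gets a 95% interval, with no governing level or null value stated; if the interval decides, power is 71–76%, not 80%

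*Protocol*

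**What the plan says.** Protocol section 10-2 (Rationale for sample size) gives the planning assumptions: "We hypothesize that the change in BIS-11 is -10.0 ± 8.0", and "the smallest clinically significant change is -5.0 by mindfulness meditation". It then states: "If the significance level is 10% on both sides and the detection power is 80%, a sample size of 18 cases is required". The target is raised slightly: "Supposing there will be some ineligible cases, the required number of cases was set to 20 cases".

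Section 10-3 (Primary outcome) sets the analysis: "Calculate the two-sided 95% confidence interval for the BIS-11 change after 8 weeks", together with a P-value from a t-test. It attaches no significance level to that P-value and does not say what value the mean change is tested against. No other section of the protocol states a decision level, says that a 90% interval is to be used, or explains why 10-2 and 10-3 use different levels.

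**The concern.** A two-sided 95% interval excludes the null value exactly when a two-sided t-test gives P below 0.05. The sample size was calculated for a test at 0.10. The only power figure in the protocol therefore belongs to a decision at 10%, while the only interval named for the primary outcome corresponds to a decision at 5%.

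Two things are at stake. First, the stated 80% may not describe the analysis from which the conclusion is drawn. Second, a result with P between 0.05 and 0.10 could be called positive by pointing to 10-2 or negative by pointing to 10-3, and nothing in the protocol settles that before the data are seen. The study is open-label with a single primary outcome, and section 1-2 says it will supply preliminary data for phase III trials, so the rule should be fixed in advance.

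**Working it through.** **Inputs.** All come from section 10-2 unless noted.
- Hypothesised mean change -10.0, SD of change 8.0.
- Smallest clinically significant change -5.0.
- Two-sided level 0.10, power 80%, required n = 18, target n = 20.
- Single arm (section 3-2), so the t-test is a one-sample test on the change.
- Two-sided 95% interval for the primary outcome (section 10-3), equivalent to a two-sided level of 0.05.

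**Formula.** With difference d from the null value, SD s and n evaluable patients, the test statistic follows a noncentral t distribution with n - 1 degrees of freedom and noncentrality (d/s) × √n. Power is the probability that this statistic falls outside ± the critical value t(1 - α/2, n - 1).

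**Step 1: reproduce the protocol's 18.** Take d = 5 and s = 8, so d/s = 0.625.

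| n | noncentrality | critical t at two-sided 10% | power |
|---|---|---|---|
| 17 | 2.577 | 1.746 | 79.4% |
| 18 | 2.652 | 1.740 | 81.6% |

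Eighteen is the first n to reach 80%, so the protocol's figure is right for its stated level. With d = 10 the same calculation needs only 6 patients. The 18 therefore rests on a 5-point difference, which can be read as a true change of -10 tested against -5, or as a true change of -5 tested against 0. The arithmetic is the same for both.

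**Step 2: same inputs, decision by the 95% interval.**

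| n | noncentrality | critical t at two-sided 5% | power |
|---|---|---|---|
| 18 | 2.652 | 2.110 | 70.5% |
| 20 | 2.795 | 2.093 | 75.5% |
| 22 | 2.931 | 2.080 | 79.8% |
| 23 | 2.997 | 2.074 | 81.7% |

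At this level 80% would need 23 evaluable patients. At n = 18 the probability of not detecting the 5-point difference is 100 - 81.6 = 18.4% at the 10% level and 100 - 70.5 = 29.5% at the 5% level.

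**Step 3: the results on which the two levels disagree.** With n = 18 and an observed SD of 8, the standard error is 8/√18 = 1.886. The 10% test rejects when the mean change lies more than 1.740 × 1.886 = 3.28 points from the null value. The 95% interval excludes the null value at 2.110 × 1.886 = 3.98 points. A mean change between 3.28 and 3.98 points from the null value gets opposite answers.

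**Step 4: dependence on the null value.** If the t-test is against 0 and the true change is the hypothesised -10, then d/s = 10/8 = 1.25 and the noncentrality is 1.25 × √18 = 5.303. Power at two-sided 5% with 18 patients is then 99.9%. The 71–76% applies to the 5-point difference and not to every reading of the hypothesised effect.

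**The case against.** The strongest reply is that section 10-3 states no significance level at all. The only one in the protocol is the 10% in 10-2, and a t-test judged at 10% can be reported beside a 95% interval kept for estimation. On that reading the 80% is correct. This stands: the 5% test is inferred from the interval, and the protocol does not exclude the other reading. It does not state that reading either, and under it the test and the interval could still disagree about the primary outcome.

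A reader might infer that the trial will certainly run a 5% test, so that its power simply is 71%. The text does not support that; the lower figure is conditional on the interval deciding. A reader might also infer that the chance of missing the planned effect rises from about 18% to about 29%. That holds for the hypothesised -10 only if the null is -5. Against a null of 0, the power for -10 is 99.9% even at 5%, and the 71% then describes the smallest clinically significant change.

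Other points in the protocol's favour: a 10% level is a legitimate choice for an exploratory pilot, and it is not disputed here. Enrolment is 20, so 70.5% is the lower end of a range. The extra two places are, however, meant to cover ineligible patients, whom section 10-1 removes from the effectiveness population. A separate statistical analysis plan might settle the level, but both conflicting figures are in the protocol and need reconciling there.

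**Conclusion.** The inconsistency is real but limited. The sample size is correct for the level stated in 10-2. What is missing is agreement between that level and the interval in 10-3, and a stated null value for the t-test. If the conclusion is drawn from the 95% interval, power for the 5-point difference used in sizing is 70.5% with 18 evaluable patients and 75.5% with all 20, against the 80% claimed. If P is judged at 0.10, the claim stands. These figures assume a one-sample t-test, an SD of change of 8 and a 5-point distance between the true change and the null value.

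**What to change.** State one governing level and the null value (0 or -5) in both sections, before the data are fixed. Either version works:

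- **Keep the 95% interval as decisive.** Restate 10-2 as: two-sided 5%; power 71% with 18 and 76% with 20 evaluable patients for a 5-point difference from the stated null, SD 8. The difference and the null must be named, because beside a hypothesised -10 the percentages cannot otherwise be interpreted.
- **Keep 10% and 80%.** State in 10-3 that P is judged at 0.10, that the 90% interval is the decision interval, and that the 95% interval is descriptive. The 18 then stands unchanged.

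The cost is a sentence or so in 10-2 and 10-3, and no added patients or assessments. The first version makes the stated power less favourable; the second labels the decision interval as 90%.
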